**Fig 1 pone.0300405.g001:**
[figure not shown]
Timeline of the study protocol. The figure illustrates the sequence of circadian stabilisation periods, in-laboratory visits, and experimental sessions over a three-week period. Key events are shown relative to the onset of the dim light session. In-laboratory visits can include nights of sleep for adaptation and multiple sessions; stabilisation happens continuously throughout the study, but are labelled in relation to in-laboratory visits.

### 2.3 Study duration & timeline

Each person participating in the study will be enrolling for a total of three weeks, consisting of continuous field measurements and one in-laboratory screening and two separate visits for control and experimental sessions.

After getting in touch with the study team, participants will first complete an online screening via the online platform REDCap [28,29]. The data from the online questionnaires or experience sampling is submitted to a REDCap server that is set up and maintained by the Chronobiology & Health team at TUM. It is set up as a virtual machine hosted by the Leibniz-Rechenzentrum der Bayerischen Akademie der Wissenschaften. If their answers comply with the inclusion and exclusion criteria, they will be invited for an in-person screening and, upon inclusion in the study, for two in-laboratory visits to take part in experiments. For an overview of the study participation, see Fig 1.

The online screening will be complemented by an in-person screening by a psychologist to confirm eligibility for the study. Since the forced-desynchrony protocol places participants in an exceptional environment, our inclusion criteria, the screening process, and procedures to ensure continued welfare are guided by suggestions from literature [30,31].

Upon inclusion in the study, participants will start a two-week long circadian stabilisation period. They will be invited for a first evening experimental session, the light exposure session, one week into the circadian stabilisation and one week before the forced-desynchrony session. Visual tests will be administered throughout the evening that achieve an experimental light exposure similar to the tasks administered during a wake period of within the forced-desynchrony session. The light exposure session also provides opportunity for the participant to get accustomed to the measurement instruments and prevent novelty or perceptual learning during the main study. After the evening session, participants will stay in the lab for a full night of sleep as their first adaptation night. Circadian outcomes from this session, including dim-light melatonin onset (DLMO) and core body temperature (CBT), as well as vigilance tests will be compared to those of an evening session under dim-light conditions. The purpose of this comparison is to quantify the potency of the light exposure during the protocol to elicit a circadian phase shift (for more information, see Sect 2.4.2).

The second laboratory visit starts with one evening session under dim-light conditions and another adaptation night when participants will have a full night of sleep (8 hours), followed by the forced-desynchrony session that involves 40 hours on a ultra-short sleep-wake cycles. Participants will enter the lab five hours before their habitual bedtime and complete a four-hour dim light session. The forced-desynchrony session starts 60 minutes after the end of the adaptation night. During the first 60 minutes, people have opportunity for personal hygiene and will be equipped with the sensors. 40 hours will be spent in constant environmental conditions, with a temperature of 20^∘^C, and no time cues are provided. The main room is lit with dim light at < 10 lux, so that light exposure is constant except during light exposure due to visual tests and during sleep. For an overview of the study period, see Fig 1.

The first ultra-short sleep-wake will start with a wake period. During wake time, all other tests will be carried out while sitting. To reach the devices, participants have to walk up within the laboratory for up to 30 meters. During wake time, light isocaloric snacks and water that are heated up to body temperature will be provided at three opportunities, mirroring breakfast, lunch, and dinner. After experiments, a remaining wake time of 30 minutes can be spent freely. The 2h30m wake period is followed by a 1h15m sleep period, that will be spent in a recumbent position. Participants will put on a light-tight sleep mask.

An overview timeline during the forced-desynchrony session is shown in Fig 2, and a more detailed timeline of single measurement blocks in Fig 3.

**Fig 2 pone.0300405.g002:**
[figure not shown]
Schematic of the 40-hour forced-desynchrony protocol. This figure illustrates the ultra-short sleep-wake rhythm, displaying the relationship between clock time, time spent in the lab since protocol start, measurement blocks, and sleep-wake cycles. The timeline begins after an adaptation night and includes a 1-hour transition period for sensor placement. Each wake period (solid lines) lasts 2h30m, followed by a 1h15m sleep period (dashed lines).

**Fig 3 pone.0300405.g003:**
[figure not shown]
Detailed timeline of a single measurement block during the 40-hour forced-desynchrony protocol. This figure outlines the sequence and duration of measurements (grey background) and activities (white background) within one 2h30m wake period, including psychophysical tests, pupillometry, physiological measurements, and scheduled meal times. The continuous measurements, core body temperature (CBT), continuous glucose monitoring (CGM), and electrocardiography (ECG), are indicated at the bottom.

### 2.4 Experimental procedure

All devices were purchased from internal funds of the investigator and were not sponsored by the manufacturer(s).

**Table 3 pone.0300405.t003:** Measurement devices.

Device	Manufacturer	Purpose	Certification
AMPBpro	SOMNOmedics, Randersacker, DE	Blood pressure measurements	
Auto Non-Contact Tonometer NT-2000	NIDEK CO., LTD., JP	Measurement of intra-ocular pressure	
e-Celsius	BodyCap, Hérouville-Saint-Clair, FR	Measurement of core body temperature using an ingestible pill	CE
FreeStyle Libre 3	Abbott Diabetes Care Ltd., UK	Continuous glucose monitoring	
iButton	Maxim/Dallas Semiconductor Corp., USA	Peripheral body temperature measurements	
Metropsis Visual Function Assessment	Cambridge Research Systems, Rochester, UK	Psychophysical measurements	
NVBL	[name], CH	Visual stimulation and pupillometry	
OCT2000	TOPCON Corporation, JP	Ocular physiology measurements, incl. corneal thickness measurements and fundus photographs	CE
PVT-192	Ambulatory Monitoring Inc., USA	Measurement of alertness	

#### 2.4.1 Screening.

An online and an in-laboratory screening will proceed the forced-desynchrony session. Participants will be included or excluded based on Table 1 and Table 2, respectively.

*Online screening.* In the online screening, participants will be asked for their age, biological sex and gender identity, and employment status. They will fill out questions on whether they are taking any medication, are smoking, have a diagnosis of epilepsy, and female-born participants will be asked about their reproductive status and menstrual cycle based on the adapted Reproductive Status Questionnaire [32]. Additionally, participants will complete a series of psychological questionnaires, delivered via the online platform REDCap. Participants will complete the Alcohol Use Disorders Identification Test (AUDIT), an instrument to examine substance and alcohol abuse, in the self-report version [33]. As an assessment of sleep habits, we will use the Pittsburgh Sleep Quality Index (PSQI), an instrument to assess quality of sleep based on usual sleep habits and sleep disturbances [34], and the Epworth Sleepiness Scale (ESS) is used to assess habitual sleepiness [35]. The Munich Chronotype Questionnaire (MCTQ) will be used to determine chronotype [36]. It determines habitual midpoint of sleep, corrected for sleep duration on free days (${MSF}_{SC}$). Only slightly early to slightly late chronotypes are admissible for reasons of scheduling group-wise participation [37]. Furthermore, we will administer the Sleep Regularity Questionnaire (SRQ) and will preferably select people with regular sleep patterns over those with more irregular patterns [38].

*In-person screening.* During the in-person screenings, participants’ physical health will be assessed using self-report questions, along with an examination by study personnel. The specific procedures encompass screening of their visual acuity using a Landolt C acuity test delivered on the Cambridge Research Systems Metropsis system, and their colour vision using HRR Pseudoisochromatic Plates. An ophthalmological exam including fundus photography and Optical Tomography images (macular image and optic disc image) will take place to confirm ocular and retinal health. The primary concern is to exclude individuals with any ocular disease or compromised visual information transmission, such as in glaucoma patients. A cup-to-disc ratio of >0.3 will lead to exclusion of the participant, as well as an intra-ocular pressure (IOP) >20 mmHg. Criteria are based on the European Guidelines for glaucoma diagnostics by the European Glaucoma Society to exclude participants with potentially diseased eyes [39]. These criteria may be conservative as higher cup-to-disc ratio does not necessarily indicate disease, especially for individuals with larger papilla size as then, automatically, the physiological papilla excavation increases. However, these criteria can be applied algorithmically, facilitating a faster decision without additional consultation. Eye dominance is determined using the Miles test [40]. In this test, a distant target is aligned binocularly through a small opening formed by both hands stretched away from the body and held steady. Then, each eye is alternatingly closed and opened to determine which monocular view of the target, seen through the aperture, matches the binocular view.

*Alcohol and drug compliance.* At the beginning of the first experimental session, the light exposure session, abstinence from alcohol and drugs will be verified using a breathalyser (Alkoholtester, ACE GmbH, Freilassing, Germany) to determine blood alcohol content (BAC), and a urine sample to determine AMP/BZD/COC/MOR/OPI/THC content (nal von minden GmbH, Moers, Germany). Participants will be asked to produce a urine sample in a collection device in a bathroom on-site. Experimenters will carry out the drug test by immersing a test strips in the urine sample. Any positive test will lead to immediate exclusion from the study. The urine sample, as well as the test strip, will be disposed of immediately on-site after testing. Documentation of the result is pseudonymised and will not contain any information for personal identification.

#### 2.4.2 Quantification of an effect of the protocol on the circadian system.

The experimental light exposure may affect the circadian system. However, indicators of the circadian systems are supposed to function as independent variable to predict visual outcomes. This may pose a problem of circularity, through which the effects of interest may be masked. The primary goal of the control sessions to estimate the effects of light exposure on circadian outcomes. During both control sessions, circadian outcomes described in Sect 2.4.7 will be measured.

To measure the effects of experimental light exposure on circadian outcomes, participants will visit the lab one week into the circadian stabilisation period, i.e. one week prior to the forced-desynchrony session, for the light exposure session. Saliva collection starts four hours prior to the participant’s bedtime, will be carried out every 30 minutes until 1 hour after habitual bedtime. For more information on the post-processing, go to Sect 2.4.7. During this time, participants will complete similar tasks as in the forced-desynchrony. The visual experiments serve to imitate the light exposure that will be experienced during the protocol. Simultaneously, they are introduced and familiarised with the experiments that will be performed during the forced-desynchrony session, and will be equipped with the continuous glucose monitor the morning after.

Furthermore, participants will enter the lab on the day before the forced-desynchrony session starts to spend an adaptation night in the lab before the protocol starts. They will enter lab approximately five hours before their habitual bedtime, 13 hours before the forced-desynchrony session. They will stay under constant dim light throughout the evening preceding the adaptation night (dim light session). Data on salivary melatonin concentration and CBT will be collected throughout the evening. Comparing indicators of circadian phase measurements from the light exposure session and the evening dim light session, we will obtain an estimate of the potency of our stimulus protocol itself in affecting the circadian system.

#### 2.4.3 Circadian stabilisation and compliance.

*Timing of homeostatic processes.* To stabilise their circadian system before entering the forced-desynchrony session, participants will start a two-week circadian stabilisation period. It is characterised by the maintenance of a strict 16:8-hour wake-sleep and light-dark schedule, and adherence to approximate meal times. Participants choose the sleep time based on their habitual sleep and wake time, and must then adhere to bed and wake times with a maximum deviation of 30 minutes.

*Caffeine, drug, alcohol and napping abstinence.* Caffeine modulates the circadian response to light [41]. To avoid possible influences, we ask participants to refrain from napping during daytime, as well as alcohol, recreational drug, and caffeine consumption seven days prior to lab visits.

*Daily questionnaire.* The 15-item consensus sleep diary serves as confirmation of sleep/wake categorisation by the actigraph [42] and will be administered via REDCap. Participants will be asked to plan notifications on their personal smartphones in order to receive prompts to complete the diary in the morning within approximately 1 hour after awakening. Participants will be asked to record their mealtime. For this purpose, they will be asked to answer questions about their meals (e.g. timing, size) and take a picture to submit it to the app.

*Compliance in ambulatory assessments.* Compliance to the circadian stabilisation will be monitored with daily logs, the sleep diary and actimetry data. Participants will be instructed to wear a light-weight actiwatch (35 g) by (ActTrust2, Condor Instruments, São Paulo, Brazil), on their non-dominant hand at all times throughout the 21 days of participation, except for when it could get wet or damaged. The device is equipped with a built-in accelerometer and light sensors. Activity and light exposure are measured in 1-min epochs. Light exposure is quantified in photopic illuminance and UV irradiance. Whether a participant is labelled awake or asleep depends on whether the activity exceeds a specified threshold for the activity counts. The data will be used to confirm compliance with circadian stabilisation, i.e. sleep and wake times, and may further be used in exploratory analysis evaluating relationship of main outcomes with regularity of light exposure (Light Regularity Index; LRI) and sleep (Sleep Regularity Index, SRI)[43].

*Metabolic activity.* We will monitor metabolic activity starting the morning after the light exposure session for a total of 14 days, thereby extending into the stabilisation period after the forced-desynchrony session. A continuous glucose monitoring (CGM) system (FreeStyle Libre 3, Abbott Laboratories, Alameda, California) is used to monitor participants’ glucose profile. The small sensor is placed on the skin of the back of the upper arm, and measures the glucose concentration in the interstitial fluid (ISF). As blood glucose levels seem to rise in food anticipation and reflect meal-time history of multiple days, they will likely not be in line with the meal-timing imposed during the ultra-short sleep/wake rhythm [44]. Participants will not have access to their glucose readings during wear time, as feedback may interfere with natural eating patterns. Glucose levels are quantified in mg/dL.

#### 2.4.4 In-laboratory visits.

During the forced-desynchrony session, participants will repeatedly undergo a battery of visual, physiological and psychometric tests during wakefulness. The experiments that will be administered during one repeatable block are described in Fig 3 and detailed below.

*Compliance during in-laboratory visit.* The experimenter will continuously monitor compliance and the successful completion of experiments. Given the demanding nature of the protocol, there is tolerance for participant’s failure to perform in individual tests. A block’s data is considered for analysis as long as one test repetition within that block is successful. However, experimentation will proceed across all modalities using light-emitting devices, even if data collection issues occur in a single modality. These devices serve a dual purpose: not only do they measure visual outcomes, but they also provide consistent light exposure > 10 lux, which is important for maintaining comparability between participants. If the experimenter fails to collect data from both primary modalities – pupillometry and psychophysics – for more than one block due to any reason (e.g., non-compliance, fatigue, tiredness), the experimental session may be aborted. This is because the increased measurement intervals would render the data unsuitable for testing circadian hypotheses.

#### 2.4.5 Pupillometric assessment of photoreceptor mechanisms.

*Maxwellian-view pupillometry.* The apparatus used for pupillometry is a custom-made six-primary binocular Maxwellian view light stimulation system [45]. The system is optimised to target different photoreceptors in isolation, including melanopsin. Light is produced by LEDs of different wavelengths (420, 450, 470, 520, 590, and 630 nm) with a bandwidth (FWHM) of approximately 20 nm each. The produced light stimulus is an annular field of 10–30^∘^ that is presented in monocular viewing conditions to the dominant eye. Participant movement will be limited using an elastic headband. The device measures pupil diameter over time based on video recordings of the respective eyes. Our main outcome is the PLR, i.e. pupil constriction upon monocular stimulation with visual stimuli of different spectral composition. Calibration of the stimulation device is done using a spectroradiometer (spectraval 1511, JETI, Jena, Germany) focused on a diffuser surface at the location of the entry pupil, and an optical power and energy meter (PM100D, Thorlabs, Bergkirchen, Germany). There will be no individual calibration procedure. Calibration of the device and calculation of the employed light spectra is described below.

*Device calibration.* The devices were carefully calibrated beforehand. Here, we describe calibration and optimization procedures we conducted in order to ensure accurate measurements for a standard observer. Calibration was done once before data collection started. Individual calibration procedures for visual experiments are not feasible in the present study. Yet, it is possible to estimate the variability in the effective contrast. To calibrate the pupillometer, it was placed in the laboratory, which provides a stable environment during the day and during experimentation (no temperature or humidity fluctuations). For the calibration process, each LED was activated and measured on separately and at different intensity settings. As experimental setup, the light beam was projected onto a ground glass optical diffuser. This diffuser, with a 1-inch diameter, was made from N-BK7 glass and featured a 220 grit surface, making it ideal for effectively scattering light uniformly across the 350-700 nm wavelength range. The diffuser was mounted in front of the light source at the pupil plane of the participants. The distance between the light source and diffuser increased the effective surface of the light beam to about 2/3-inch diameter. The spectroradiometer was positioned close enough to the diffuser so that the effective surface area extended the receptive field of the Jeti spectroradiometer. Using the device’s control software, we set LED intensities at 0%, 1%, 2%, and 5% steps. We then measured the remaining intensity spectrum in 5% increments, up to 10%, resulting in a total of 23 different intensity levels. We obtained spectral intensity distributions with a spectral resolution of 1 nm. We validated our spectral radiance measurements independently with a powermeter: we measured the power emitted at all the light intensities of each LED. An optical powermeter was connected via a cylinder-shaped applicator to the lenses of the device, in similar proximity as the pupil would be. This way, the light beam emitted from the device fell in the receptive field of the powermeter, while it was shielded from external light sources. The experimental light conditions were generated using *PySilSub*: as background, we specified all LEDs to be at half maximum intensity, and selected a constrained numerical optimization procedure. The software also requires a so-called calibration as input, which is with power-adjusted light spectra at different intensities generated by normalizing the measured spectra with the empirically measured power.

*Silent substitution stimuli.* Spectral composition of the light stimuli is varied to achieve silent substitution of the photoreceptor mechanisms of interest. Briefly, this means the activity of one or more photoreceptors is selectively modulated while the activation of other photoreceptors is kept constant [13,46–48]. While rods are saturated photopic light levels [49,50], stimuli will modulate melanopsin and cone activation for five conditions: (1) joint modulation of all photoreceptors (Light flux, melanopsin-containing ipRGCs, L-, M-, and S-cones) (2) joint modulation of all cones while keeping melanopsin activity constant (L+M+S) (3) selective modulation of melanopsin activation (Mel, constant of L, M, S activation) (4) selective modulation of S-cone activation (S) (5) selective modulation of the red-green colour channel activity (L–M). Comparing the four listed conditions against the Light flux condition, we will determine the unique circadian variation of the photoreceptor mechanisms.

The action spectra we used for the calculation of the silent substitution spectra stem from the default settings of the *PySilSub* package: the cone fundamentals of the macula from [58], and the melanopic and rhodopic action spectra [59] for a 32-year-old standard observer. We did not perform an age-adjustment considering different lens transmittance, when calculating the silent substitution spectra. We will simulate the response and report the residual variation, or deviation between obtained and target contrast, in the contrast of retinal mechanisms and photoreceptors after silencing. We will disclose the effective precision of photoreceptor by calculating the so-called *contrast splatter* using the same method as [13].

*Experimental procedure.* During the forced-desynchrony session, every participant then completes 11 blocks, with a test and a test repetition in each block. Each test encompasses an adaptation period and 25 trials. Participants adapt to a photopic background ($60\;{cd/m}^{2}$) for four minutes, to ensure rod saturation. The adaptation period is followed by 25 trials per test, where participants will view sinusoidal light modulations with a frequency of 0.4 Hz, interspersed with white baseline stimulation. 0.4 Hz was selected to measure pupil responses in a temporal regime in which all photoreceptors are likely responsive [13]. The experimental stimulus presentation takes place for five seconds, followed by a period of baseline stimulation with white light of 13 seconds, yields a total trial duration of 17 seconds. One test consists of 25 trials, five repetitions of each experimental condition; conditions are counterbalanced using an m-sequence. One test takes about 12–15 minutes, amounting to about 30 minutes per block for pupillometric assessment. A short break temporally separates the two tests.

*Control for rod intrusion.* As recent literature as shown that rods phototransduction may recover even at high light levels and based on temporal modulation [50,51], we will conduct a control experiment to test whether rods escape saturation. The control experiment will take place after data collection of the main study has been completed and will include a different set of participants than the participants in the main trial. Using pupillometry, we will evaluate the response to silent substitution stimuli targeting rods at light levels comparable to the planned experimental condition and with the same temporal frequencies. The results of this control study will be reported and discussed in the context of the results seen in the main study in subsequent publications.

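### The powermeter readings said to validate the pupillometer spectra also scale its calibration, and the planned precision report describes no measured check of the final stimuli

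*Protocol article*

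**What the plan says.** All of this is in section 2.4.5 of the protocol article unless stated otherwise.

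- **Validation.** Under Device calibration: "We validated our spectral radiance measurements independently with a powermeter". The coverage was complete for single LEDs: "we measured the power emitted at all the light intensities of each LED". No agreement result or tolerance between the two instruments is given.
- **Reuse.** The same paragraph describes the calibration supplied to PySilSub as "generated by normalizing the measured spectra with the empirically measured power". The optimiser uses it to choose LED settings around a background with every LED at half its maximum.
- **Timing.** "Calibration was done once before data collection started". The support offered for stability is the laboratory, "which provides a stable environment during the day and during experimentation".
- **Planned precision report.** Under Silent substitution stimuli: "We will simulate the response and report the residual variation, or deviation between obtained and target contrast". Contrast splatter will be computed by a method that is only cited. The text does not say which spectra feed the simulation.
- **Role of the melanopsin stimulus.** H1d (section 1.4) concerns the pupil response to melanopsin modulation with cone activation held constant. The sequential Bayes factor that can stop recruitment is computed on the melanopsin-dependent pupil model (section 2.1.3).
- **Admitted limits.** Section 3.1 concedes small residual contrast on receptors that should be silent, and attributes it to differences between individuals. Device error is not mentioned.

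**The concern.** Silent substitution depends on the relative output of the six LEDs. Once the spectra are normalised by measured power, the powermeter sets the scale of each LED and the spectroradiometer supplies mainly the spectral shape. The relative scale thus rests on the readings that are presented as the check.

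The precision report would be expected to close that gap, but its obtained contrast is simulated. A simulation run on the calibration that produced the settings returns the optimiser's own residual, plus whatever observer variation the cited splatter method adds. It carries no information on whether the device emits what the calibration says. No described step measures the background or the modulated stimuli with several LEDs on together, and none repeats the calibration, although participants are tested one at a time (section 2.2), up to twelve of them.

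What is at stake is attribution. The protocol hypothesises that cone-driven pupil responses are themselves rhythmic (H1a–H1c), and it chose 0.4 Hz because all receptor classes are likely to respond there. Cone contrast leaking into the melanopsin condition could carry a cone rhythm into H1d, and dividing by the light-flux response (section 2.5.2, eq. 1) does not remove it. The reported precision could still look clean.

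**Working it through.** **1. The plan's own figure.** The only checkable number in the procedure is the count of 23 intensity levels. The levels 0, 1, 2 and 5%, then 5% steps from 10% to 100%, give 4 + 19 = 23, which matches. With the upper limit as printed (10%) the count would be 5, so that limit looks like a slip for 100%. Nothing below depends on it.

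**2. Why a simulation on the same calibration cannot see LED-specific error.** For receptor k,

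contrast_k = Σ(g_i · s_ki · d_i) / Σ(g_i · s_ki · b_i)

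Here g_i is true output over calibrated output of LED i, s_ki is the response of receptor k to LED i, d_i is the modulation and b_i = 0.5 is the background. Simulating from the calibration sets every g_i = 1, so cone contrast in the melanopsin condition is zero by construction before observer variation is added. If all g_i share one value, it cancels between numerator and denominator. Only errors that differ between LEDs matter.

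**3. Inputs for an illustration.** From the protocol: six LEDs at 420, 450, 470, 520, 590 and 630 nm, about 20 nm bandwidth each, background at half maximum. Assumed: equal LED power; generic pigment templates peaking at 560, 530, 430 and 488 nm (L, M, S, melanopsin) without lens or macular filtering; independent LED gain errors of SD 1, 2 or 5%. The documents give no LED error figure. The stimulus maximises melanopsin contrast with L = M = S = 0; 20,000 draws were made per SD.

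**4. Results.** Nominal melanopsin contrast is 22.0%. RMS unintended cone contrast:

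| LED-specific SD | L | M | S | Simulated from the same calibration |
|---|---|---|---|---|
| 1% | 0.26% | 0.34% | 0.51% | 0 |
| 2% | 0.52% | 0.67% | 1.02% | 0 |
| 5% | 1.3% | 1.7% | 2.6% | 0 |

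Relative to the melanopsin contrast, the S-cone leak is 0.51/22.0 = 2.3% at SD 1% and 2.6/22.0 = 12% at SD 5%. A common 10% gain error leaves the cones at 0 and melanopsin at 22.0%.

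**5. A single worked case.** Take gains of 1.05, 0.97, 1.03, 0.98, 1.02 and 0.96, and let the optimiser design from the resulting wrong calibration. The simulation reports L = M = S = 0 and melanopsin 21.5%. The true contrasts are L −0.2%, M +0.5%, S −2.0% and melanopsin 21.6%.

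**6. Sensitivity to the assumptions.** With a lens filter and three different LED power balances, nominal melanopsin contrast is 24–34%, and the 95% range of mean L+M contrast is about ±0.5–0.7% at SD 1% and ±2.6–3.3% at SD 5%. The model in step 4 gives RMS mean L+M contrast of 0.29% and 1.44%; multiplied by 1.96 these are 0.57% and 2.8%, inside those ranges. A further run with assumed templates gives RMS cone contrast of 0.2–0.5% at SD 1% and 1.1–2.6% at SD 5%, against 20–29% melanopsin contrast.

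**The case against.** **The validation may have been genuine.** The powermeter is a second instrument with its own optical arrangement, and the claim concerns the spectral radiance measurements, not the finished calibration file. Comparing the instruments before normalisation would be a real check of output and linearity, and later scaling does not undo it. This stands. A reader might infer that the claim of independence is false; the documents do not show that. What they show is that the readings became an input, so they do not independently check the file that was actually used.

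**The simulation's input is not stated.** A reader might infer that the reported precision can reveal no device error at all. That goes too far: the protocol does not name the spectra used, and the cited splatter method is not at hand. The point is conditional on the simulation using the one calibration described.

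**An article condenses.** Bench checks may exist elsewhere. Fair, but the article does state how obtained contrast will be produced, namely by simulation, and a measured alternative is better and cheap. That criticises a stated method and does not rest on missing detail.

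**The effect on conclusions is limited.** A fixed LED error, or slow drift between participants, creates no 40-hour rhythm within a person, and the models carry person-specific intercepts. The L+M+S, S and L–M conditions are measured in the same blocks, so a cone rhythm should be visible there. Both arguments stand. They confine the harm to attribution, but they do not tell the reader how much cone contrast the melanopsin stimulus contained.

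**Conclusion.** The point holds in a limited form. The readings offered as validation are also a calibration input, and the planned precision report describes no measurement of the final stimuli. If, as is likely, the simulation uses the single pre-study calibration, its residual will not reflect LED-specific gain error, non-additivity or drift.

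The plausible size is roughly 0.2–2.6% RMS unintended cone contrast against about 20–34% melanopsin contrast. This rests entirely on assumed receptor templates, LED power balances and an LED-specific error of SD 1–5%. It has not been translated into pupil amplitude, the ratio R or the Bayes factor, so no change in a conclusion or in stopping is demonstrated.

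A reader might go on to infer that device error could manufacture the circadian effect. The documents do not support that: a fixed leak produces no rhythm by itself, a gain error common to all LEDs cancels, and the separate cone conditions help interpretation. What is weakened is the attribution of an H1d effect to melanopsin, and that matters somewhat more because the same model drives the stopping rule. This is an inexpensive improvement to the precision report, not a flaw that invalidates the design.

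**What to change.** - With the spectroradiometer already listed in section 2.4.5, measure the background and both extremes of each of the five conditions with all LEDs driven together: 1 + 2 × 5 = 11 spectra. Do this once now and once at the end of data collection.
- Compute obtained contrast and contrast splatter from these measured spectra, and report them alongside the simulated values.
- Report the agreement between spectroradiometer and powermeter before normalisation, or delete the word claiming independence.

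Measuring before every participant and re-optimising the settings mid-study are not needed. The cost is an estimated few hours of bench time with no participant burden. The reported precision may look slightly less favourable.
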